### Recruitment

The SPIRIT checklist is presented in table 1. The first participant was enrolled in June 2023. Before the surgery, all planned surgical patients underwent screening of their medical history, physical examination and radiological examination to assess eligibility. For those who were eligible and willing to participate, a detailed explanation of the potential risks and benefits of participating in the study was provided, and all questions were answered. All participants signed a written informed consent form before surgery, one for both the investigator and the participants.

**Table 1 T1:** The schedule of enrolment, interventions and assessments based on the SPIRIT checklist.

Timepoint	Study period									
	Screening and enrolment	Trial treatment period	Follow-up period							
	−1 w	0 (Operation)	1w	1m	3m	6m	1y	1.5y	2y	3y
Enrollment										
Collection of informed consent	X									
Demographic and clinicopathological data	X									
Medical history	X									
Physical examination*	X				X	X	X	X	X	X
Radiological examination†	X				X	X	X	X	X	X
Histological or cytological confirmation of breast cancer	X									
Interventions										
Omit SLNB‡		X								
Breast surgery		X								
Adjuvant systemic therapy (if implemented)		X								
Radiotherapy (if implemented)		X								
Assessments										
Arm circumference measures			X	X	X	X	X	X	X	X
Bioelectrical impedance			X	X	X	X	X	X	X	X
Questionnaire Quick DASH			X	X	X	X	X	X	X	X
Questionnaire FACT B			X	X	X	X	X	X	X	X
Survival outcome			X	X	X	X	X	X	X	X
Disease status			X	X	X	X	X	X	X	X
Adverse events			X	X	X	X	X	X	X	X

* Physical examination, including breast and axillary lymph node palpation.

† Radiological examinations, including breast and axillary ultrasound, MRI, PET-CT, and [18F]-FDG PET-MRI inspection projects.

‡ SLNB, sentinel lymph node biopsy.

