### Clinical intervention and follow-up

After obtaining informed consent, axillary surgery will be omitted for eligible patients, and BCS or mastectomy (allowing breast reconstruction) will be voluntarily selected by the patient under the premise of ensuring therapeutic efficacy. Patients receiving BCS must undergo whole breast irradiation (WBI) after surgery, and postoperative adjuvant therapy and other treatments will be performed according to clinical guidelines.

Multiple timepoints will be established for dynamic follow-up at baseline and up to 3 years postoperatively, with a comprehensive and objective assessment of breast cancer-related lymphoedema (BCRL) using multi-segmental arm circumference measurements and bioelectrical impedance analysis at baseline, 1 week, 1, 3, 6, 12, 18, 24, and 36 months postoperatively, respectively. Patients will be administered a QoL questionnaire using the validated FACT-B (Version 4.0) and Quick DASH at the same time point.^30 31^ BCRL incidence and QoL will be subjectively assessed by patients using patient-reported outcomes (PROs).

Patients who discontinue or withdraw from the trial for any reason during the trial can be treated with disease-specific therapies, including supplemental SLNB, ALND, radiotherapy and other therapies as appropriate, after obtaining informed consent.

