##### 1. Relative volume change (RVC) of >10% in the affected upper limb

The upper limb volume will be calculated using the method of multisegmental arm circumference measurement. Five points will be taken to measure arm circumference. The midpoint of the ulnar styloid process at the distal end of the arm will be the starting point and measurements will be taken every 10 cm from this point towards the proximal end of the arm up to 40 cm. These five measurement points enable the limb to be divided into four truncated cones. The volume of each limb segment is calculated using the following formula:

V=[h (C12+C22+C1C2)]/12π

where C1 and C2 denote the arm circumference at the upper and lower points of the measurement segment, h=10 cm. The volume of the entire upper limb is the sum of the volumes of the segments. RVC is calculated using the following formula^32^:

RVC=[(A2×U1])/(U2×A1)]−1

where A1 indicates the volume of the affected upper limb at baseline, A2 indicates the volume of the affected upper limb at a specific time point, U1 represents the volume of the unaffected upper limb at baseline and U2 indicates the volume of the unaffected upper limb at a specific time point. The incidence of BCRL will be assessed at each follow-up timepoint.

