##### 2. Bioelectrical impedance analysis (BIA)

The single-frequency bioimpedance analysis (SFBIA) ratio is defined as the ratio of the unaffected to the affected side.^33^ The SFBIA ratio of both upper limbs at 1 kHz and 5 kHz will be measured using bioelectrical impedance technology. The diagnostic criteria in this study will refer to the findings of Liu Miao *et al*. BCRL recognition is superior when the threshold is set at the mean+2 SD for healthy women.^34^ BCRL will be diagnosed when any one of the following is fulfilled:

The dominant affected arm SFBIA ratio at 1 kHz of >1.067.The nondominant affected arm SFBIA ratio at 1 kHz of >1.043.The dominant affected arm SFBIA ratio at 5 kHz of >1.068.The nondominant affected arm SFBIA ratio at 5 kHz of >1.044.PROs: Patients will be followed up with questionnaires using FACT-B (Version 4.0) and Quick DASH during the same period as the BCRL assessment. The FACT-B scale will be used to assess changes in QoL in breast cancer patients with SLNB omission from baseline to 3 years after surgery. The Quick DASH scale will be used to assess changes in arm morbidity from baseline to 3 years after surgery.Locoregional recurrence (LRR), local recurrence (LR), regional recurrence (RR)： LR is defined as the time from surgery to the appearance of a tumour in the ipsilateral breast, chest wall or skin at the surgical scar. RR is defined as the time from surgery to the appearance of a tumour in the lymphatic drainage area of the affected side, including the axillary, supraclavicular, subclavicular and internal mammary lymph node regions. Clinical recurrence suggested by imaging or other investigations requires a definitive diagnosis by cytology or histopathology. Suspected recurrent lesions for which histological or cytological examination is not possible will be submitted to the Data Safety Monitoring Board (DSMB) for independent review.

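### Table 1 schedules no baseline for arm circumference, bioimpedance, Quick DASH or FACT-B, although the text, the RVC formula and the questionnaire endpoints require one

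*Protocol article*

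**What the plan says.** **Schedule (protocol article, Recruitment, Table 1).** There are ten time columns: −1 week, operation, and eight follow-up visits from 1 week to 3 years. The rows "Arm circumference measures", "Bioelectrical impedance", "Questionnaire Quick DASH" and "Questionnaire FACT B" are blank in the first two columns and marked in the other eight.

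**Text (Clinical intervention and follow-up).** Lymphoedema is to be assessed "using multi-segmental arm circumference measurements and bioelectrical impedance analysis at baseline, 1 week, 1, 3, 6, 12, 18, 24, and 36 months postoperatively". The two questionnaires are tied to the same time points.

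**Volume criterion (Secondary endpoints, item 1).** RVC = (A2 × U1)/(U2 × A1) − 1, "where A1 indicates the volume of the affected upper limb at baseline"; U1 is the corresponding baseline volume of the unaffected arm.

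**Bioimpedance criterion (item 2).** The ratio of unaffected to affected arm is compared with fixed cut-offs at 1 kHz and 5 kHz, set by arm dominance. The stated reason is that "BCRL recognition is superior when the threshold is set at the mean+2 SD for healthy women". No term refers to the patient's own preoperative ratio. Meeting either the volume or the bioimpedance criterion is enough for a diagnosis of breast cancer-related lymphoedema (BCRL).

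**Questionnaires (same section).** FACT-B and Quick DASH are both analysed as change from baseline to 3 years.

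**The concern.** The schedule and the endpoint definitions disagree about whether four measures are taken before surgery. A preoperative arm volume or questionnaire score cannot be obtained once the operation has been done. The missing-data plan cannot help either: last observation carried forward has nothing earlier than baseline to carry.

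Patients have been enrolled since 28 June 2023, so any loss grows with each patient treated according to the table. Arm morbidity and quality of life are the benefits that the Introduction claims for omitting sentinel node biopsy, so these endpoints carry the benefit side of the trial.

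**Working it through.** **1. Schedule against text.**

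| Measure | Table 1: −1 week | Table 1: operation | Table 1: 1 week to 3 years | Time points in text |
|---|---|---|---|---|
| Arm circumference | blank | blank | 8 marks | 9, with baseline |
| Bioimpedance | blank | blank | 8 marks | 9, with baseline |
| Quick DASH | blank | blank | 8 marks | 9, with baseline |
| FACT-B | blank | blank | 8 marks | 9, with baseline |

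The difference is 9 − 8 = 1, and the missing time point is baseline. The blanks are not a shift from PDF reading: in the same table, physical examination falls at −1 week and then 3 months to 3 years, and breast surgery falls at operation, as one would expect. No other row fills the gap. The rows marked at −1 week are consent, demographic and clinicopathological data, history, physical examination (footnoted as breast and axillary palpation), radiology and histology.

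**2. What needs the baseline.**
- RVC: yes, through A1 and U1.
- FACT-B and Quick DASH change: yes, by definition.
- Bioimpedance criterion: no. It is a single-visit ratio against a fixed cut-off.
- Combined BCRL: in part. A woman positive on bioimpedance can be classified. For a woman negative on bioimpedance, the volume half cannot be evaluated.

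**3. How much RVC depends on baseline.** The formula rearranges to RVC = (A2/U2)/(A1/U1) − 1. Take assumed follow-up volumes A2 = 2150 mL and U2 = 2000 mL, so A2/U2 = 1.075.
- A1/U1 = 0.95: 1.075/0.95 − 1 = 13.2%, above the 10% cut-off.
- A1/U1 = 1.00: 1.075/1.00 − 1 = 7.5%, below it.
- A1/U1 = 1.05: 1.075/1.05 − 1 = 2.4%, well below it.

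The same follow-up measurements give opposite diagnoses, depending on the value that the table does not schedule.

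**4. Why the 1-week value is no substitute.** If the affected arm is already 5% swollen at 1 week (assumption), an RVC of 10% against that value corresponds to 1.05 × 1.10 = 1.155, a true increase of 15.5%.

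**5. Women above the bioimpedance cut-off without lymphoedema.** Assume that ratios in such women are normal, with the healthy-women mean and SD. Then P(Z > 2) = 0.0228 per frequency at one visit. Two frequencies apply to each woman.
- Perfectly correlated frequencies: 2.3%.
- Independent frequencies: 1 − (1 − 0.0228)² = 4.5%.
- Between-frequency correlation of 0.95 (assumed): about 3%.

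Among 311 women this is 0.0228 × 311 ≈ 7 to 0.0451 × 311 ≈ 14, and about 0.03 × 311 ≈ 9 at the assumed correlation. A preoperative bioimpedance measurement would identify the women who exceed the cut-off before any surgery.

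**The case against.** The strongest reply is that the text asks for baseline in several places: the follow-up section, the RVC definition and both questionnaire endpoints. Against that stands one table, in a single-centre trial where the same team wrote the text and takes the measurements. A clerical omission is the natural reading. Nothing in the document shows that a baseline was missed, and invasive disease-free survival and the sample size are untouched. All of this stands, and it limits the point to an inconsistency in the schedule of secondary endpoints. It does not remove the point, because a schedule table is a working document and a value missed because of it is lost for good.

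A reader might infer more in three ways, none of which the document supports.

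- *That the lymphoedema endpoint cannot be computed at all.* The bioimpedance half needs no baseline, so the failure is confined to RVC, the RVC half of the combined rule and the questionnaire changes.
- *That the bioimpedance rule alone would produce a lymphoedema rate like the 4% to 8% quoted in the Introduction after sentinel node biopsy.* That requires counting a woman as a case if she is positive at any of eight visits. A simulation on that basis gives 5.6% to 11.0% for assumed visit-to-visit correlations of 0.95 to 0.70. The RVC section, however, says incidence is assessed at each follow-up time point, and the protocol states no ever-positive rule. Per visit the figure is about 3%, below the quoted range. The quoted rates also differ in timing; the 8% is a 6-month figure.
- *That a positive bioimpedance result should be confirmed at a second consecutive visit.* This would redefine the endpoint, would lose transient cases and those first seen at 36 months, and is not needed to resolve the contradiction.

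**Conclusion.** The contradiction is real and affects four measures. Table 1 gives eight time points where the text gives nine, and the missing one is the baseline on which RVC and both questionnaire endpoints are defined. If the table is followed, those quantities cannot be computed and cannot be rescued later.

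The cause is probably an omission in the table. Only secondary endpoints are at risk, and how many patients lack baseline data, if any, cannot be told from the document.

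A smaller, related point also holds. Since the bioimpedance criterion ignores the preoperative ratio, asymmetry present before surgery would be counted as new lymphoedema. About 3% of women without lymphoedema would exceed a cut-off at a given visit, with a range of 2.3% to 4.5% over the possible between-frequency correlations from one to zero. This rests on assumed normality and on the healthy-women reference applying to these patients. The RVC and 1-week illustrations rest on assumed volumes and swelling; they show the dependence on baseline and do not predict its size in this trial.

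**What to change.** 1. In Table 1, add a mark at −1 week for arm circumference, bioimpedance, Quick DASH and FACT-B. Each row then has nine time points and agrees with the text.
2. Check now that every patient enrolled since June 2023 has these preoperative data, and report how many do not.
3. State that the 1-week value will not stand in for a missing baseline. For such patients, RVC and questionnaire change are missing and should be reported as missing.
4. Report RVC-based and bioimpedance-based BCRL separately as well as combined. Report how many women already exceed a bioimpedance cut-off before surgery, so that they are not counted as incident cases.

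The cost is four marks in a table, a short data check and a few lines of analysis wording. The text already calls for the measurements, so no new assessment is added, and the sample size and error rates do not change. Delay is the main cost, because each patient operated on without a baseline is a permanent loss to these endpoints.

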### Trial participants and inclusion/exclusion criteria

#### Inclusion criteria

The study enrolled participants based on strict inclusion and exclusion criteria. Patients who meet all of the following inclusion criteria will be eligible for inclusion:

Female patients aged 18–70 years.Pathologically confirmed invasive breast cancer (regardless of he pathological type), breast cancer of ≤3 cm and scheduled to undergo breast surgery.Negative axillary lymph nodes as assessed by physical examination and two or more radiological exams, including axillary ultrasound, such as breast MRI, breast PET-CT or breast PET/MRI.All patients are required to undergo immunohistochemical staining for oestrogen receptor, progesterone receptor, human epidermal growth factor receptor 2 (HER2), Ki-67 proliferation index and further fluorescence in situ hybridisation should be performed in HER2 2+cases.Good compliance, normal comprehension and the ability to receive treatment and follow-up as required.ECOG score 0–1.Patients who volunteered for this study signed the informed consent form.

#### Exclusion criteria

Patients meeting any of the following exclusion criteria will be excluded from the study:

Bilateral, lactating, pregnant breast cancer.Clinical or imaging confirmation of distant metastasis.Previous history of malignant tumour or neoplasm.Previous surgery on the affected axilla or history of surgery affecting the function of the upper extremity.History of radiotherapy to the breast or chest.Positive pathological margins after BCS or mastectomy.Severe coagulation disorder, serious systemic disease or an uncontrollable infection.Aspartate aminotransferase (AST), alanine aminotransferase (ALT) of ≥1.5-fold of the upper limit of normal value, alkaline phosphatase of ≥2.5-fold of the upper limit, total bilirubin of ≥1.5-fold of the upper limit, serum creatinine of ≥1.5-fold the upper limit and left ventricular injection fraction (LVEF) of <50% on cardiac ultrasound.Inability to complete the full course of follow-up adjuvant therapy as prescribed by the doctor for various reasons.No personal freedom or independent civil capacity.Presence of mental disorders, addictions, etc.Not eligible for enrollment as judged by the investigator.

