**Methods and analysis:**

The OMSLNB trial is a prospective, single-arm, non-inferiority, phase II, open-label study design involving female breast cancer patients with a tumor of ≤3 cm in diameter, who are considered axillary lymph-node-negative based on two or more radiological examinations, including axillary lymph node ultrasonography. Eligible patients will avoid axillary surgery but will undergo breast surgery, which is not limited to breast-conserving surgery. The trial begins in 2023 and is scheduled to end in 2027. The primary endpoint is 3 year invasive disease-free survival (iDFS). The secondary endpoints include the incidence of breast cancer-related lymphoedema, patient-reported outcomes, locoregional recurrence, local recurrence and regional recurrence. It is expected that the 3 year iDFS in patients undergoing SLNB is about 90%, combined with a non-inferiority cut-off of 5%, 80% power, 95% CIs, 0.05 test level, and 10% loss to follow-up rate, the planned enrollment is 311 patients. All enrolled patients will be included in the intention-to-treat analysis.

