## Methods and analysis

### Trial design and setting

This study is a prospective, noninferiority, single-arm, phase II open-label clinical trial conducted at the First Hospital of Nanjing Medical University. Patients with unilateral invasive breast cancer (tumor ≤3 cm) and assessed as cN0 will be eligible for inclusion. The enrolled patients are required to complete two or more imaging tests, including axillary ultrasound assessed as axillary lymph-node-negative, and other tests including MRI, PET-CT and [18F]-FDG PET/MRI. Patients with suspected lymph node metastasis will be directly excluded from enrollment. All patients are required to undergo preoperative coarse needle aspiration or intraoperative mass biopsy for pathologically confirmed invasive breast cancer (regardless of pathological type). Subsequently, surgeons will be required to provide a detailed explanation of the potential benefits and risks associated with the omission of SLNB to eligible patients. Before any surgical procedure is undertaken, patients must provide written informed consent. Following consent, patients will undergo BCS or mastectomy (allowing for breast reconstruction) without axillary surgery, with a postoperative follow-up of 3 years.

This clinical study will be conducted following the relevant provisions of the Declaration of Helsinki, and it was registered at http://www.clinicaltrials.gov (NCT number: NCT05935150). The study was reported according to the Standard Protocol Items: Recommendations for Interventional Trials (SPIRIT) checklist.^29^ The detailed flow chart of the study is shown in figure 1.

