### Endpoints

#### Primary endpoint

The primary endpoint of this trial is 3 year invasive disease-free survival (iDFS), defined as the time from surgery to local recurrence, regional recurrence, distant metastasis, infiltration of the contralateral breast cancer or death from any cause, whichever occurs first.

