### Statistical analysis

The primary analysis will use an intention-to-treat (ITT) analysis. For categorical variables, the χ2 test or Fisher’ s exact test will be used, and the data will be presented as totals, percentiles and frequencies. For continuous variables, descriptive statistics will be analysed using mean, SD or median and IQR. Independent samples t-tests will be used for normally distributed continuous variables, and nonparametric tests will be used for skewed data to analyse the results. Kaplan–Meier curves and log-rank tests will be used to determine the statistical significance of variables in the survival outcome categories (iDFS) and survival curves will be plotted. The prognostic significance of variables will be assessed using univariate and multivariate COX risk regression analyses. HR and 95% CI will be calculated. For each statistical analysis, a p value <0.05 will be considered statistically significant.

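### The positive-margin exclusion can be met only after SLNB has been omitted and the iDFS clock has started, which contradicts analysing all enrolled patients; the adjuvant-therapy exclusion is ambiguous on the same point

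*Protocol article*

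**What the plan says.** All references are to the protocol article.

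- **Exclusion criteria.** The list opens with "Patients meeting any of the following exclusion criteria will be excluded from the study". It includes "Positive pathological margins after BCS or mastectomy" and "Inability to complete the full course of follow-up adjuvant therapy as prescribed by the doctor for various reasons".
- **Recruitment and Table 1.** "All participants signed a written informed consent form before surgery". Table 1 places screening and enrolment at −1 week, and the operation with omission of SLNB at time 0.
- **Trial design and setting.** "Following consent, patients will undergo BCS or mastectomy (allowing for breast reconstruction) without axillary surgery".
- **Primary endpoint.** 3-year iDFS is "defined as the time from surgery to local recurrence" or another listed event, so time zero is surgery.
- **Analysis set.** Abstract, Methods and analysis: "All enrolled patients will be included in the intention-to-treat analysis". Statistical analysis: "The primary analysis will use an intention-to-treat (ITT) analysis".
- **Sample size calculation.** Expected 3-year iDFS 90%, margin 5 points (limit 85%), power 80%, α 0.05, 10% dropout, N = 311.

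**The concern.** Margin status after the operation is a post-treatment finding. A patient who meets the criterion has already consented, been enrolled, had axillary surgery omitted and started to contribute iDFS time. The eligibility section puts this patient out of the study, while the abstract puts the same patient in the primary analysis. Both cannot be followed.

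The conflict matters more here than in a randomised trial. There is one arm and a fixed limit, so no control group passes through the same filter. If patients removed after time zero have worse iDFS than those kept, the estimate rises and the test leans towards non-inferiority. The estimate would also describe a group that cannot be identified when the decision is made, because SLNB is omitted before final margins are known. The article says that a successful result would lead to a larger phase III trial.

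**Working it through.** **1. Order of events**

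| Step | Time | Section |
|---|---|---|
| Consent, screening, enrolment | −1 week | Recruitment, Table 1 |
| Breast surgery, SLNB omitted | 0 | Table 1, Trial design and setting |
| iDFS clock starts | 0 | Primary endpoint |
| Margin criterion can be met | after 0 | Exclusion criteria |

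No section says that enrolment is confirmed only after final pathology, or that a patient excluded for margins stays in follow-up and analysis.

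The adjuvant criterion has no fixed place in this order. Inability could be foreseen at screening, and the inclusion criteria already ask for a patient able to undergo treatment and follow-up. Yet the wording refers to completing a prescribed course, for unspecified reasons and with no time limit, so it can also be applied later.

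**2. The plan's own figure**

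One-proportion test, limit 0.85, true value 0.90, one-sided 5%, power 80%:

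n = [1.645·√(0.85·0.15) + 0.842·√(0.90·0.10)]² / 0.05² = 282.1, so 283.

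With dropout: 283/0.9 gives 315, and 283 × 1.1 gives 312. The smallest exact binomial n is 281 (249 or more event-free needed, size 4.97%, power 81.1%), and 281/0.9 gives 313. The stated 311 is reproduced to within about 1%. Sidedness is not stated; one-sided 2.5% with the variance taken at 0.90 also gives 283.

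**3. Illustration of the bias**

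Assumptions, none of them from the article: a share m of operated patients is excluded after surgery, their 3-year iDFS is q, and the true iDFS in all operated patients is 85%, so non-inferiority should be declared at most 5% of the time. iDFS is treated as a proportion, as in the sample size section.

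iDFS in those kept: x = (0.85 − m·q)/(1 − m).

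Start from 281, keep n = 281·(1 − m) rounded down, find the smallest r with P(X ≥ r | n, 0.85) ≤ 0.05, then compute P(X ≥ r | n, x).

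| m | q | x | n kept | r | Size at 85% | False non-inferiority |
|---|---|---|---|---|---|---|
| 2% | 80% | 85.1% | 275 | 244 | 4.6% | 5.1% |
| 5% | 75% | 85.5% | 266 | 236 | 4.9% | 7.8% |
| 10% | 75% | 86.1% | 252 | 224 | 4.6% | 11.6% |
| 10% | 70% | 86.7% | 252 | 224 | 4.6% | 17.3% |

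Rounding n to the nearest integer (275, 267, 253) gives 5.1%, 7.5%, 11.2% and 16.7%. Holding n at 281 gives 5.5%, 8.0%, 12.9% and 19.3%. An exact one-sided 2.5% test at the n in the table gives 2.2%, 3.7%, 5.7% and 9.1%.

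When q = 85% there is no bias; when q is above 85% it reverses.

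**4. Power**

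Power = Φ[(0.05·√n − 1.645·√0.1275)/√0.09]. With n = 311 × 0.9 = 279.9 it is 79.7%. A further 5% or 10% excluded after surgery gives 77.6% or 75.4%.

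**The case against.** The best defence is that the eligibility list governs entry and the ITT statements govern analysis, so a margin-positive patient might be recorded as ineligible and still be analysed. The article also does not define enrolment in so many words. This softens the point without removing it. Exclusion from the study is the stated consequence, nothing says that follow-up continues, and Table 1 places enrolment before the operation. This is a conflict between two statements in the article itself, so a separate analysis plan would not remove it.

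A reader might infer that both criteria can be known only after surgery, and that patients who stop adjuvant therapy because of recurrence, toxicity or death are therefore removed. The article does not support that. The adjuvant criterion speaks of inability, not failure. It stands among items checked at screening and has a baseline counterpart in the inclusion criteria. Recurrence and death are counted as iDFS events, and no section removes a patient for having one. Such removal is a possible use of loose wording, not a stated rule.

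A reader might also take the bias as established. The article gives no positive-margin rate and no outcome for such patients, and does not say whether the criterion still applies once margins have been cleared. That objection stands in full, and in mild scenarios the effect is close to nil.

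**Conclusion.** The contradiction on the margin criterion is real and rests on the article's own text. Followed as written, the eligibility section selects patients after treatment and after time zero in a single-arm test against 85%. For the adjuvant criterion the finding is only that its timing is not fixed.

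The direction of bias, towards non-inferiority, holds if the excluded patients do worse than the rest. Its size cannot be determined from the article. Under the assumed rates, false non-inferiority runs from about 5% (essentially nominal) to about 17% for a nominal one-sided 5% test. The wording should be corrected. The sample size is not affected.

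**What to change.** Reconcile the exclusion criteria with the ITT statement:

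1. Limit eligibility to what is known before surgery. Either take the margin criterion out of the eligibility list, or state that meeting it neither ends follow-up nor removes the patient from analysis. Word the adjuvant-therapy criterion as inability foreseen before surgery.
2. Define the ITT set as every consented, preoperatively eligible patient operated on with SLNB omitted, followed for iDFS from surgery.
3. Put any exclusion of margin-positive patients in a sensitivity analysis.
4. Report how many patients have been excluded under either criterion after surgery since enrolment began in June 2023, and follow them for iDFS where consent allows.

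How positive margins are treated clinically is outside this change.

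Cost: a protocol amendment, one sensitivity analysis and possibly a slightly less favourable iDFS estimate. N stays at 311. Had exclusions after surgery been kept on top of the 10% dropout, 283 evaluable patients would require about 283/(0.9 × 0.95) = 331 enrolled at an assumed 5% excluded, or 283/(0.9 × 0.90) = 350 at 10%.
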